### Statistical Analysis

2.15

Primary analyses will be conducted on an intention‐to‐treat basis. Treatment effects for continuous outcomes will be estimated using linear regression models, adjusted for stratification variables study site and baseline ulcer size, and where relevant also baseline level of the outcome. For time‐to‐event outcomes, time to 50% healing and time to complete healing, we will conduct survival analysis, including Kaplan–Meier curves and Cox proportional hazards models (adjusted for study site and baseline ulcer size). Multiple imputation by chained equations will be used to handle missing outcomes data (except for censored time‐to‐event data). Per‐protocol analysis will also be performed on all participants who are > 90% capsule compliant. Complete case analysis will also be conducted to examine if results were sensitive to the approach for handling missing data. Statistical analyses will be conducted using Stata/SE 17.

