### Intervention

2.2

Adults with a DFU will be recruited and undergo placebo or vitamin C supplementation in a double‐blind, randomised manner. The treatments will consist of oral ingestion of either vitamin C (500 mg ascorbic acid per capsule, two capsules per day; so, a total of 1 g/day) or placebo (microcrystalline cellulose capsule, two capsules per day) for 8 weeks. A placebo group as the comparator is considered the most rigorous test of treatment efficacy for evaluating a medical therapy in a double‐blind RCT [27]. Participants will be instructed to take one capsule in the morning and one capsule in the evening alongside meals. All outcome measures will be conducted at the beginning (baseline) and then at 8 weeks of treatment. Outcome measures for wound healing will also be recorded at fortnightly visits to the clinic during the 8‐week treatment period (Figure 1). The trial will conclude for each participant at 8 weeks or beforehand if the patient undergoes amputation or withdraws consent.

All participants will continue to receive usual standard of care throughout the trial. Standard care was defined according to the IWGDF Practical Guidelines (2023 update) [28] and comprised core evidence‐based prevention and management practices for DFD. This included routine risk‐based foot screening using structured assessments for neuropathy, peripheral artery disease, deformity, callus, pre‐ulcerative lesions, and any history of ulceration or amputation. Participants also received education on daily foot inspection, protective footwear use, foot hygiene, and prompt escalation for any foot concerns. Standard care additionally involved appropriate offloading and therapeutic footwear to reduce plantar pressure, as well as timely ulcer classification and management using best practice wound care and coordinated evaluation of infection or peripheral artery disease within a multidisciplinary model.

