#### Ulcer Assessment

2.7.3

Ulcer assessments and measurements will be collected in person by two qualified and experienced (6 and 15 years) Podiatrists at Monash Health who are members of the research team. The number of current ulcers will be recorded. If the participant has more than one ulcer, the largest ulcer will be chosen as the index ulcer [38]. Thereafter, data will only be collected on the index ulcer for this study. Ulcers will then be classified via the Site, Ischaemia, Neuropathy, Bacterial Infection, and Depth (SINBAD) score [39], the WIfI (Wound, Ischaemia, foot Infection) classification [39] and aetiology (neuropathic, ischaemic or neuroischaemic). Ulcer duration and whether the wound is probing to bone, tissue microbiological culture results and any treatment as part of standard care, such as treatment for infection, revascularisation or pressure offloading will be recorded [38]. Amputation outcomes will also be collected, and participants undergoing amputations will be considered not to have healed ulcers.

Ulcer size will be determined by measuring the ulcer length and width with a paper ruler and the depth with a metal probe to calculate the volume in mm^3^. This approach is widely used in a clinical setting [40, 41, 42]. Bedside excisional debridement of nonviable tissue will be conducted prior to wound measurements [28]. Ulcer length will be recorded as the maximum diameter of the ulcer, while ulcer width will be taken as the perpendicular diameter to ulcer length. The ulcer area will be calculated using the ellipse formula [41] and ulcer volume calculated as ulcer area × ulcer depth. A digital image of the wound will also be captured. Interobserver reliability of standard ruler measurements has previously been reported to be excellent for both estimated area (Intraclass correlation coefficients (ICC) 0.98, 95% CI 0.97–0.98) and depth using a probe (ICC 0.93, 95% CI 0.90–0.95) [41]. Also, at the beginning of the study, both Podiatrists underwent the same training according to standard operating procedures for wound measurement that we developed for the trial based on the IWGDF Practical Guidelines (2023 update) [28] and the reliability of wound measurement study by Lasschuit et al. [41].

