#### Primary Outcome

2.8.1

The primary outcome measure is the percentage reduction in ulcer size (ulcer volume in mm^3^) at 8 weeks, compared to baseline. We based our treatment length on the intervention published by Gunton et al. who found in an RCT of 16 participants that percentage ulcer healing at 8 weeks (percentage reduction in ulcer size) was significantly better in people following vitamin C treatment at median 100% compared with −14% following placebo [22]. The minimal clinically important difference is considered a 50% improvement in ulcer size after 4 weeks of treatment and is a robust predictor of complete healing in DFUs [53] and is also considered a large effect size [22, 54]. The ulcer will be considered 100% healed when the epithelium is completely intact. Outcome measures and time points are shown in Figure 1.

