### Handling of Withdrawals

2.12

When scenarios of participant withdrawal occur for reasons such as voluntary withdrawal, medical withdrawal (including undergoing amputation), protocol violation and/or adverse events, the participant's data will be included in an ‘intention to treat’ analysis (as detailed below in 2.15). No data substitution will be applied for reporting of adverse events or intervention adherence.

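### Amputees count as not healed, yet section 2.15 as written imputes their week-8 ulcer volume and no stated primary analysis scores amputation as failure

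*Protocol article*

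**What the plan says.** Five statements in the protocol article bear on this.

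- Section 2.8.1 (Primary Outcome): "The primary outcome measure is the percentage reduction in ulcer size", measured as ulcer volume at 8 weeks against baseline. It is a continuous outcome.
- Section 2.7.3 (Ulcer Assessment): "participants undergoing amputations will be considered not to have healed ulcers".
- Section 2.2 (Intervention): "The trial will conclude for each participant at 8 weeks or beforehand if the patient undergoes amputation or withdraws consent". An amputee therefore has no week-8 measurement.
- Section 2.12 (Handling of Withdrawals) lists "medical withdrawal (including undergoing amputation), protocol violation and/or adverse events" among the reasons for withdrawal. It places such participants' data in the intention-to-treat analysis and refers to section 2.15 for the details.
- Section 2.15 (Statistical Analysis): "Multiple imputation by chained equations will be used to handle missing outcomes data", with one exception, for censored time-to-event data. It adds: "Complete case analysis will also be conducted to examine if results were sensitive to the approach for handling missing data".

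Section 2.15 does not mention amputation.

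**The concern.** The article sets an outcome rule for amputees in one place and sends the same people to a missing-data rule in another. The two rules treat the event differently. If the site of the index ulcer is amputated, the week-8 volume does not exist; it is not a value that someone failed to record. Chained-equation imputation in its usual missing-at-random form supplies the volume expected in similar people who kept the foot, which is often a partial reduction. Complete case analysis drops the amputee altogether. The per-protocol analysis selects on capsule compliance and assigns no failure value either.

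At stake is the primary treatment difference. Amputation is among the worst outcomes an ulcer can have, and under the stated rules it enters the primary estimate as average-to-poor healing or not at all. With 40 participants per arm, 5%, 10% and 15% amputated are 2, 4 and 6 people, so a handful of events can move the result.

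**Working it through.** **1. The plan's own figures reproduce.** Section 2.14 gives d = 0.80, two-sided α = 0.05, 90% power and 34 per arm. A two-sample t-test with n = 34 per arm has 90.2% power, and 68 / 0.85 = 80. For time to 50% healing, 70% censoring in control means a 30% event rate. With hazard ratio 3.5 the treated rate is 1 − 0.7^3.5 = 0.713, giving 34 × (0.300 + 0.713) = 34.4 events. Freedman's formula at 34 events gives z = √34 × 2.5/4.5 − 1.96 = 1.28, or 90.0% power. Nothing below changes the sample size. The issue is what is estimated.

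**2. Inputs that the article does not give.** There is no 8-week amputation rate. The Introduction's 20% of ulcers leading to amputation has no time horizon, and section 2.4 excludes people already proceeding to amputation. I assume 5% to 15% for the primary outcome, where 15% equals the whole withdrawal allowance in section 2.14, and 2% to 15% for the time-to-event check.

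**3. Primary outcome, simple arithmetic.** Let a be the proportion amputated and m the mean imputed reduction among amputees, with arm 1 vitamin C and arm 0 placebo. Against amputees scored at 0%, imputation raises an arm's mean by a × m, so the treatment difference shifts by a1×m1 − a0×m0. Assume non-amputees average 60% on vitamin C and 20% on placebo, with amputees imputed at their arm mean. The difference under imputation is then 60 − 20 = 40 points.

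| Amputated, vitamin C / placebo | Difference, failure = 0% | Shift: a1×60 − a0×20 |
|---|---|---|
| 5% / 5% | 38 | 3 − 1 = 2 |
| 10% / 10% | 36 | 6 − 2 = 4 |
| 15% / 15% | 34 | 9 − 3 = 6 |
| 15% / 5% | 32 | 9 − 1 = 8 |
| 5% / 15% | 40 | 3 − 3 = 0 |

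**4. Primary outcome, simulation.** Placing amputees at their arm mean ignores the fortnightly volumes that an imputation model could use. A simulation allowed for this: 40 per arm, SD 50 and a true difference of 40 points (d = 0.8), imputation on arm and the week-4 value (correlation 0.6 with week 8), and amputees selected for poor early healing.

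| Amputated, vitamin C / placebo | Imputed | Failure = 0% | Shift |
|---|---|---|---|
| 5% / 5% | 40.93 | 38.88 | 2.05 |
| 10% / 10% | 40.08 | 36.20 | 3.88 |
| 15% / 15% | 39.57 | 33.71 | 5.86 |
| 15% / 5% | 40.28 | 34.03 | 6.25 |
| 5% / 15% | 39.36 | 37.58 | 1.78 |

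Across these scenarios 54% to 69% of imputed amputee values were positive reductions, and 19% to 33% reached a 50% reduction or more.

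**5. Time to 50% healing, if amputees are censored at amputation.** This uses constant hazards and the 8-week event rates from step 1, and compares 1 minus Kaplan–Meier with the cumulative incidence when amputation precludes healing.

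| Arm | 1 − Kaplan–Meier | Cumulative incidence, 2% to 15% amputated | Overstatement |
|---|---|---|---|
| Control | 0.300 | 0.297 to 0.274 | 0.3 to 2.6 points |
| Treated | 0.713 | 0.703 to 0.636 | 1.0 to 7.7 points |

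**The case against.** The best defence is that the sections can be read together. Section 2.7.3 already fixes an amputee's healed status, and section 2.15 imputes only what is missing. For complete healing at week 8 the status is then known and nothing is imputed. That stands: a reader might infer that the plan credits amputees with complete healing, but the text does not require it.

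Second, a reader might infer that amputees are censored at amputation in the Kaplan–Meier and Cox analyses. The article does not say so. It follows only by inference from the early end of follow-up and the exception for censored data. Even then a Cox model would estimate a valid cause-specific hazard ratio; the trouble would lie mainly in reading 1 minus Kaplan–Meier as the proportion healed.

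Third, the not-healed rule gives no number for a percentage reduction, so for the primary outcome one could speak of an unspecified value and leave it to an analysis plan, which may exist but is not shown. This stands only in part. Section 2.12 names amputation and refers it to section 2.15, and section 2.15 states a general rule with no exception that would cover the primary outcome. An analyst who follows the text would impute.

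Fourth, the size rests on assumed rates, and with few amputations it is small. That stands.

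**Conclusion.** The point holds for the continuous primary outcome: as written, an amputee's week-8 reduction is imputed as if the foot had been kept, and neither the main analysis nor the stated sensitivity analysis scores amputation as failure. For the time-to-healing outcomes it is probable but inferred.

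Under assumed amputation rates of 5% to 15%, the shift in the treatment difference is about 0 to 8 points by simple arithmetic and about 2 to 6 points in simulation, on an assumed difference of 40 points.

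It is tempting to say that the bias favours whichever arm has more amputations. The formula does not support this. With equal rates the shift favours the arm that heals better. In the 60%/20% example it is zero at 5% on vitamin C against 15% on placebo, and it turns against vitamin C only when the placebo rate is more than three times the vitamin C rate.

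These figures take 0% reduction as the failure value. That is not a worst value, because ulcers can enlarge: section 2.8.1 cites a placebo median of −14%. A lower failure value would widen the gap within each arm.

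**What to change.** In sections 2.12 and 2.15, state that amputation involving the index ulcer is an outcome event and not missing data, and limit imputation to values missing for other reasons. Then, by outcome:

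- **Primary outcome:** fix before unblinding a failure value no better than no improvement, for example the worse of 0% and the last observed change. Give a worst-rank analysis and the imputed analysis as sensitivity analyses.
- **50% and complete healing at week 8:** count amputees as non-responders.
- **Time to 50% and to complete healing:** keep amputees who have not yet had the event in the risk set, event-free, to week 8, or treat amputation as a competing event.

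The cost is a few sentences. No new data are needed, since section 2.7.3 already provides for recording amputations, and the sample size is unchanged. The downside is that the primary estimate becomes a composite that includes amputation as failure, and the report should say so. Section 3.1 expects data collection to finish by June 2026. A rule chosen after unblinding would be open to challenge.

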## Discussion

3

The aim of this RCT is to evaluate the efficacy of oral vitamin C supplementation on wound healing in people with DFU. There is now sufficient evidence from us and others that low vitamin C status is highly prevalent in patients with DFUs [20, 21, 22, 23], and this is likely associated with sub‐optimal wound healing and higher risk of amputation [21, 23].

Our RCT has several strengths. First, to minimise the risk of bias we are using independent researchers for allocation concealment and randomisation. This ensures that both investigators and participants remain blinded during data collection and analysis. Additionally, we have tried to limit the exclusion criteria so that the study findings will likely be generalisable to other patients with DFU who attend a high‐risk foot service. Also, the outcome measures are all routinely utilised in high‐risk foot services, further enhancing the study's clinical relevance. Should the findings be positive, the intervention has strong potential for widespread implementation due to its low cost, commercial availability and minimal risk of side effects.

Our study has some limitations to be considered. The 8‐week duration may be insufficient to capture complete ulcer healing in all participants. Additionally, the study is also not likely sufficiently powered to address other questions, including if there is a threshold of plasma vitamin C concentration above which there is no benefit of supplementation for wound healing. Furthermore, it is beyond the scope of this trial to establish the efficacy of vitamin C supplementation on other clinically important outcomes such as amputation rates and mortality. However, percentage changes to wounds after just 3–4 weeks are sufficient to provide robust predictions of complete ulcer healing [53, 56]. Thus, the duration of treatment is sufficient to properly address the aims of this study and provide clinically relevant outcomes.

An important consideration in our study is the dose of vitamin C. While the 1 g/day oral dose of vitamin C is high compared to the recommended daily intake of 40 mg/day, it is a common commercially available dose and proposed as a ‘prudent’ upper level of intake by the NHMRC [19]. Regarding tolerability, no studies have reported any adverse effects with several months' treatment of 1 g/day vitamin C supplementation in humans (reviewed in [19]).

### Trial Status and Plan for Dissemination of Findings

3.1

This study has commenced recruitment, and the first participant completed their baseline assessment in January 2025. We anticipate data collection from all participants to be completed by June 2026. We anticipate the trial will produce one high‐quality publication and we will communicate our findings at relevant scientific meetings. We are also capturing several secondary and exploratory outcome measures to provide pilot data to inform future studies and provide opportunities for future research using an approach consistent with the objectives from the Diabetes Feet Australia national strategy [57].

## Data Availability

There are currently no plans for sharing data or future use of this data.
